**Secondary outcome **			
Asthma related quality of life in children	miniPAQLQ	Online questionnaire	Enrolment, 6 and 12 months
Asthma control	ACT or C-ACT	Online questionnaire	Enrolment, 6 and 12 months
Medication adherence	BMQ	Online questionnaire	Enrolment, 6 and 12 months
Patient and family reported experiences *Parental satisfaction* *travel*, *costs*, *missed school/work*, *asthma-self management knowledge *	Purpose designed questionnaire	Online questionnaire	Enrolment, 6 and 12 months

*Demographics*. Key demographic data including age, gender, language spoken at home, country of birth, parent/carer level of education, Socio-Economic Indexes for Areas (SEIFA) data and indigenous status will be collected from electronic medical records and the baseline questionnaire.

*Healthcare utilisation*. Researchers will focus on 3 key areas of healthcare utilisation: i) GP visits, ii) ED visits, and iii) hospital admission. This will be collected from electronic records and questionnaires.

*Asthma control*. Level of asthma control will be assessed using the Asthma Control Test (ACT; for children ≥ 12 years old) or Childhood Asthma Control Test (C-ACT; children 5–11 years old). These validated tools consist of 5–7 Likert-type scale questions, with a 4-week recall, assessing the frequency of shortness of breath and general asthma symptoms, use of rescue medication, the effect of asthma on daily functioning, and overall self-assessment of asthma symptom control. The total score range is 0–27 (C-ACT) and 0–25 (ACT) respectively, with a score on either test less than 19 indicating uncontrolled asthma [22].

*Quality of life*. Quality of life of the child will be assessed by using the miniPAQLQ validated tool [23], which consists of 13 questions in three domains (activity limitation, symptoms, and emotional function). The activity limitation domain includes 3 questions relating to play, sports and other daily activities; symptoms domain has 6 questions on cough, wheezing and nocturnal awakening; emotional function domain contains 4 questions associated with items such as being frightened, frustrated or feeling different, being irritable or worried, etc. Scores for each item range from 1 (maximum impairment) to 7 (no impairment). Overall score will be calculated by dividing the total scores with 13.

*Medication adherence*. Medication adherence will be assessed by using the Brief Medication Questionnaire (BMQ) [24] which consists of 12 screening questions of three domains (medication regimen, belief, and recall) with 1-week recall. The regimen domain has five items, with scores from 0 (adherence) to 1 (potential non-adherence). The belief domain has 2 items, with scores from 0 (no belief barrier) to 2 (belief barriers present). The recall domain has five items, with scores from 0 (no recall barriers) to >1 (recall barriers present). The questionnaire assesses patient adherence and barriers to adherence.

*Oral corticosteroid use*. Parents/Carers will be asked to recall retrospectively the number of days their child with asthma has required oral corticosteroids (e.g., prednisolone) in the preceding 6 months. Where possible, corroboration will be obtained on review of their electronic medical records if oral corticosteroids have been prescribed within a hospital setting.

#### School/Work absence

Parents/Carers will be asked at 6-month intervals to recall number of days their child has been absent from school/childcare or they have been absent from work due to their child’s asthma

*Sample size calculation*. Based on existing literature that shows 2.8% of paediatric ED attendances is asthma-related, we will be able to recruit at least 317 children from three LHDs for the impact assessment. Allowing for 15% attrition this will assure 270 participants for final analysis to detect a rate ratio of 2.6 in the mean number of asthma-related ED presentations before and after intervention, 80% power and 5% significance (two-sided). This calculation was based on the power calculation method for rate ratio of Poisson-distributed count data for a single sample setting.

Participants will be recruited from all eligible sites within each LHD. Recruitment of participants from each LHD will be proportional to the eligible catchment population within the specific LHD.

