Systematic review and meta-analysis from our team have shown that a multicomponent comprehensive asthma model of care that includes i) asthma self-management education, ii) active care coordination connecting patients/families with acute, primary and community-based services, and iii) in-home environmental assessment can reduce asthma hospital presentations by 80% [11]. Subsequently we evaluated a co-developed integrated model of asthma care, co-designed with parents and professionals, at Sydney Children’s Hospital (SCH), which included the provision of a standardised asthma discharge pack for children and parents containing an individualized Asthma Action Plan, information pack and discharge instructions (including recommended follow-up with a GP), streamlined appointments with a GP post-discharge from the hospital, and text message reminders to parents reminding them to follow-up with GP and encouraging attendance to an asthma education session. This model of care led to a 56% reduction in number of children who presented frequently to the ED with asthma [14]. Although the model of care was effective in a large metropolitan children’s hospital, its value in rural areas cannot be assumed and translation of the successful model into rural areas requires robust evaluation.

Therefore, leveraging digital technology and building on our existing work on paediatric asthma, we will implement and evaluate a comprehensive and flexible model of care that ensures standardisation of asthma discharge from hospital, active care coordination between acute and primary care services, establishes linkage with a child’s school/childcare services and delivers home-based follow up services to provide optimal health outcomes in children with asthma living in rural NSW.

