#### Data analysis

Interrupted time series (ITS) analysis will be used to assess the change in the time series patterns (intercept and slope) of health service use before and after intervention.

ACT score, asthma related quality of life, medication adherence, parent and child quality of life and family reported experiences will be compared at enrolment, 6 and 12 months after enrolment into the service. We will describe the outcomes at each time point using mean, standard deviation, median, and inter-quartile range. Since each participant will have three repeated measures over time, we will use multi-level regression analysis to examine the effect of the intervention on these outcomes, including in the models, a fixed effect for the intervention status (0 = pre-intervention, 1 = 6-month post-intervention, 2 = 12-month post-intervention) and calendar time of enrolment into the intervention for each participant, as well as a random effect of the Local Health District (LHD) to explore the degree of variation in the intervention effect by LHD. Our final model will exclude the random term in the presence of a statistically non-significant random effect. We will also consider participants are clustered within each LHD and use generalised estimating equations (GEE) approach in the regression analysis to account for the clustering.

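### The stated detectable rate ratio of 2.6 with 270 children implies a baseline ED rate that is implausible for this population, has no stated direction, and is not calculated for the planned interrupted time series

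*Protocol article*

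**What the plan says.** The sample size paragraph under Aim 1 says "we will be able to recruit at least 317 children from three LHDs for the impact assessment", and then "Allowing for 15% attrition this will assure 270 participants for final analysis". The target is stated as "to detect a rate ratio of 2.6 in the mean number of asthma-related ED presentations before and after intervention, 80% power and 5% significance"; the test is two-sided. The method is named: "This calculation was based on the power calculation method for rate ratio of Poisson-distributed count data for a single sample setting". The paragraph gives no baseline rate, no time unit and no direction for the ratio.

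Four other parts of the article bear on this figure:
- Box 1 requires one or more ED presentations, or one or more admissions, in the last 12 months.
- Hypotheses and aims expects a reduction in unscheduled presentations.
- Aim 1, Data collection compares up to 5 years before enrolment with up to 12 months after it, using the same children's records.
- Aim 1, Data analysis sets out how service use will be analysed: "Interrupted time series (ITS) analysis will be used to assess the change in the time series patterns (intercept and slope").

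**The concern.** The article gives the method, the power, the significance level, the number analysed and the effect. Together these fix the baseline mean on which the calculation must rest. If that mean does not fit the children being enrolled, the stated effect is not what the design can detect.

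This is the only power statement for the impact assessment, and it concerns one of the three primary measures. A reader who takes it at face value, as a fall, would think that only reductions of about 62% (1 − 1/2.6) are within reach and that reductions of 30% to 50% are not. The figure would then be a poor guide to interpreting a null result.

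**Working it through.** **Inputs.** From the sample size paragraph: n = 270, ratio 2.6, 80% power, two-sided 5% (z = 1.960 and 0.842), single-sample Poisson. From Box 1: at least one ED presentation or admission in 12 months. Assumed, because the article does not state it: a pre-intervention rate of 0.2 to 1.5 ED presentations per child-year. The lower end is one presentation in 5 years.

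**Step 1, attrition.** 317 × 0.85 = 269.5, so 317 enrolled and 270 analysed agree.

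**Step 2, baseline implied by 270 and 2.6.** For post/pre ratio R, the expected number of baseline events needed is

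E = (1.960 + 0.842·√R)² / (R − 1)², with n = E / (baseline mean per child).

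- R = 2.6: (1.960 + 0.842 × 1.612)² / 1.6² = 3.317² / 2.56 = 4.30. Then 4.30 / 270 = 0.016 per child.
- R = 1/2.6 = 0.385: (1.960 + 0.842 × 0.620)² / 0.615² = 2.482² / 0.379 = 16.27. Then 16.27 / 270 = 0.060 per child.

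So the stated pair corresponds to about 4 or 16 baseline ED presentations among all 270 children over the counted period. Under Box 1, the same 270 children have at least 270 qualifying contacts (ED presentations or admissions) in the preceding year.

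**Step 3, the same method at assumed baselines.**

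| Pre-rate per child-year | Children needed for a 2.6-fold fall (16.27 / rate) | Detectable post/pre ratio with n = 270 |
|---|---|---|
| 0.2 | 81 | 0.64 |
| 0.5 | 33 | 0.77 |
| 1.0 | 16 to 17 | 0.83 |
| 1.5 | 11 | 0.86 |

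The third column solves E(R) / rate = 270 for R below 1. In reductions, it runs from 36% at a rate of 0.2 to 14% at 1.5.

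**Step 4, pre-rate estimated and counts overdispersed.** Here the pre-rate is estimated from 12 months of the same 270 children's records, and the two counts are treated as independent:

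var(log R) = φ·[1/(270μ) + 1/(270μR)], with |log R| = (1.960 + 0.842)·√var.

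μ is the pre-mean and φ the overdispersion factor; both are assumed. The detectable effect as a before/after ratio (1/R) is:

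| μ | φ = 1 | φ = 2 | φ = 3 |
|---|---|---|---|
| 1.5 | 1.23 | 1.35 | 1.46 |
| 1.0 | 1.29 | 1.46 | 1.61 |
| 0.5 | 1.46 | 1.76 | 2.08 |
| 0.25 | 1.76 | 2.45 | 3.50 |

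For means of 0.5 to 1.5 the range is about 1.2 to 2.1, that is, falls of 19% to 52%. A ratio of about 2.6 appears at a mean of 0.25 with φ near 2.2.

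**Step 5, match to the analysis.** The power calculation compares one post-intervention mean with a known constant. The planned analysis estimates changes in level and slope around an estimated pre-intervention series. Steps 3 and 4 are also mean-ratio calculations, so they show the scale of the discrepancy and are not the power of the interrupted time series.

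**The case against.** The strongest reply is that a condensed article need not print the baseline rate or time unit, and that a full protocol may hold them. If the counting period were one month, the implied 0.060 would be 0.060 × 12 = 0.72 per child-year, which is plausible. The formula would then return 270 for a 2.6-fold fall. That may be how the figure arose, but it uses one month of follow-up per child where the plan gives up to 12. With a 12-month mean of 0.72, the same formula at n = 270 detects a ratio of 0.81, so 2.6 would still not describe this design.

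Two further parts of the reply stand. A baseline near 1 cannot be asserted: Box 1 accepts an admission instead of an ED presentation, and a 5-year average could be well below 1. Low rates with overdispersion can also reach 2.6 when the pre-rate is estimated (Step 4). That calculation, however, is not the single-sample Poisson method that the article names.

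A reader might infer several stronger things that the article does not support.
- **That 2.6 points the wrong way.** Read as before over after, it is a 62% fall, in the hypothesised direction. The fault is only that the direction is unstated.
- **That the effect is over-optimistic because the metropolitan model achieved 56%.** The article says "This model of care led to a 56% reduction in number of children who presented frequently to the ED with asthma", which is a different measure. The same Background section also cites an 80% reduction in hospital presentations from a meta-analysis, so 62% lies between the two.
- **That the 2.8% in the same paragraph is the baseline and fails to give 270.** It is the asthma share of paediatric ED attendances, used to support recruitment, and not a rate per child.

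**Conclusion.** The point holds in a limited form. Under the method that the article names, 270 children and a ratio of 2.6 require a baseline mean of about 0.016 or 0.060 presentations per child. This cannot be squared with the eligibility rule and up to 12 months of follow-up. Even at the low assumed rate of 0.2 per child-year, the method needs about 81 children for a 2.6-fold fall. The calculation also does not match the planned analysis, and the direction of the ratio needs stating.

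The conclusion about the named method does not depend on a particular baseline within 0.2 to 1.5 per child-year. The size of the replacement figure does depend on it, and on the overdispersion. It would be wrong to conclude that the study is too small: over most of the assumed range, 270 children detect smaller effects than the article claims. It would also be wrong to conclude that no reasonable assumptions give 2.6. A less favourable figure, 2.6 or more, arises at pre-means of about 0.25 or lower with overdispersion of about 2 or more.

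**What to change.** Keep 317 enrolled and about 270 analysed. Replace the rate ratio of 2.6 with the detectable post/pre ratio, below 1, for asthma-related ED presentations. Derive it under the interrupted time series model that will be fitted to the counts, with the pre-intervention rate estimated rather than taken as known. State the assumed baseline rate, its time unit and the overdispersion, and show the result over a small range of each. If the full protocol already holds the baseline used, quote it and recalculate for the whole follow-up period.

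The cost is a recalculation and a few sentences of revised text. It needs no additional children, visits or data. The restated figure may be less favourable than the single-sample results once estimation of the pre-rate and overdispersion are allowed for, and should be reported as it falls.

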#### Data analysis

Interrupted time series (ITS) analysis will be used to assess the change in the time series patterns (intercept and slope) of health service use before and after intervention.

ACT score, asthma related quality of life, medication adherence, parent and child quality of life and family reported experiences will be compared at enrolment, 6 and 12 months after enrolment into the service. We will describe the outcomes at each time point using mean, standard deviation, median, and inter-quartile range. Since each participant will have three repeated measures over time, we will use multi-level regression analysis to examine the effect of the intervention on these outcomes, including in the models, a fixed effect for the intervention status (0 = pre-intervention, 1 = 6-month post-intervention, 2 = 12-month post-intervention) and calendar time of enrolment into the intervention for each participant, as well as a random effect of the Local Health District (LHD) to explore the degree of variation in the intervention effect by LHD. Our final model will exclude the random term in the presence of a statistically non-significant random effect. We will also consider participants are clustered within each LHD and use generalised estimating equations (GEE) approach in the regression analysis to account for the clustering.

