### Aim 1: Impact assessment

#### Data collection

Changes in health service use for participating children will be evaluated by comparing the period of up to 5 years prior to their enrolment into the program (pre-intervention) and the period of up to 12 months following enrolment (post-intervention). This information will be gathered primarily from electronic care records at baseline (retrospectively gathering data on health service use in previous 5 years) and 12 months post-enrolment. Five years data pre-enrolment will be used to account for disruption from the COVID-19 pandemic.

As we are following up participants through time in each site, the pre- intervention time period of health service use for each participating site will serve as its own control for the post-intervention time period of health service use, that is, temporal control.

*Outcomes measures*. All outcome measures for the impact assessment will be assessed at baseline, 6 months, and 12 months post-intervention (Table 1). We will measure the changes over time (i.e., pre-intervention at baseline and post-intervention at 6-month and 12-month), and differences between intervention and temporal control groups on all indicators.

**Table 1 pone.0304711.t001:** Outcome measures of the impact assessment.

Outcome	Measure(s)	Source	Time point

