**Primary outcome **			
Health service use	• Hospital admissions • ED attendances • GP visits	Linked routinely collected medical records	Pre and post intervention

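### The primary interrupted time series reports two parameters with no deciding contrast, and the stated 80% power belongs to a third quantity, the simple before/after rate ratio

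*Protocol article*

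**What the plan says.** Table 1 of the protocol article makes health service use the primary outcome, with three measures ("Hospital admissions • ED attendances • GP visits"), assessed before and after intervention. The Aim 1 Data analysis section gives its analysis in one sentence: an interrupted time series will "assess the change in the time series patterns (intercept and slope) of health service use before and after intervention". The Discussion repeats the method without choosing between the two parameters.

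The Aim 1 sample size calculation expects 317 recruits and, after 15% attrition, 270 children "to detect a rate ratio of 2.6 in the mean number of asthma-related ED presentations before and after intervention", with 80% power at two-sided 5%. The method is described as the "power calculation method for rate ratio of Poisson-distributed count data for a single sample setting". No baseline rate is given. The Data collection section sets a pre-enrolment history of up to 5 years and a post-enrolment period of up to 12 months.

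**The concern.** Three quantities are in play for one primary question. The intercept change is the jump at enrolment. The slope change is the difference in trend afterwards. The sizing quantity is the ratio of mean counts before and after. The intercept change equals the sizing quantity only if there is no pre-enrolment trend and no slope change.

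The 80% power is therefore attached to a comparison that the analysis section does not plan. A reader also cannot tell what result would count as success. The design makes it plausible that the two coefficients part company: the discharge pack and text reminder act within days, while virtual home visits may come up to 3 months after discharge. An early drop that wanes gives a favourable intercept and an unfavourable slope. A delayed benefit may show only in the slope.

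**Working it through.** **Inputs from the article.** 317 recruited, 15% attrition, 270 analysed, rate ratio 2.6, 80% power, two-sided 5%; up to 5 years before and 12 months after enrolment.

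**Assumptions.** Monthly counts in time from enrolment, Poisson, no overdispersion or autocorrelation, no pre-enrolment trend, and baseline rates as stated at each step.

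**1. Attrition.** 317 × 0.85 = 269.5, and 270 / 0.85 = 317.6. The stated figures reproduce to rounding.

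**2. The 270.** A single-sample Poisson calculation is n = [(1.960 + 0.842√RR)/(RR − 1)]² / λ0, with λ0 the baseline count per child.
- RR = 2.6: (3.317/1.6)² = 4.30, so n = 270 implies λ0 = 4.30/270 = 0.016.
- RR = 1/2.6: (2.482/0.615)² = 16.27, so λ0 = 16.27/270 = 0.060.

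Without λ0 the 270 cannot be reproduced. Other common formulas imply 0.012 to 0.044 (RR 2.6) or 0.050 to 0.115 (RR 1/2.6). Using the article's 2.8% as λ0 gives 154 or 581 by the formula above, not 270.

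**3. Precision of the planned parameters.** The model is log μ(t) = β0 + β1·t + β2·post + β3·post·t. The covariance is (X′WX)⁻¹ with W = diag(μ). The 12-month average contrast is β2 + 6β3. Under no effect, with 270 children at 1 presentation per child-year (22.5 a month):

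| Pre months | SE simple log ratio | SE level | SE average | Level/slope correlation | P(either significant at 5%) |
|---|---|---|---|---|---|
| 12 | 0.086 | 0.173 | 0.228 | 0.00 | 0.098 |
| 24 | 0.075 | 0.149 | 0.134 | −0.50 | 0.091 |
| 60 | 0.067 | 0.134 | 0.087 | −0.76 | 0.081 |

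The variance ratio of level to simple is 4.02 in every row. That ratio and the last two columns do not depend on the assumed rate.

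**4. Power at the rate that makes the 80% true.** Power = Φ(|log RR|/SE − 1.96), for a constant step. Example: RR 2.6, 60 pre months, SE 0.739, so 0.9555/0.739 − 1.96 = −0.67, power 0.25.

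| Step, λ0 | Pre months | Level | Average | Simple two-period ratio |
|---|---|---|---|---|
| 2.6, 0.016 | 12 | 0.13 | 0.08 | 0.39 |
| 2.6, 0.016 | 60 | 0.25 | 0.38 | 0.74 |
| 1/2.6, 0.060 | 12 | 0.17 | 0.16 | 0.53 |
| 1/2.6, 0.060 | 60 | 0.21 | 0.52 | 0.63 |

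The last column shows that part of the loss comes from the single-sample method treating the before-rate as known; the rest comes from moving to the level parameter. Other single-sample formulas widen the level range to 0.11 to 0.30. A two-period formula would give 0.29 to 0.58. Counts this small make the normal approximation rough, but no version reaches 0.80 for the level change.

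**5. Power at 1 presentation per child-year.** For a step of 1/2.6, level-change power is 0.985 (12 pre months) or 0.997 (60).

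**6. Disagreement.** With 60 pre months and 1 presentation per child-year, a drop to 0.6 that returns to 1.0 by month 12 gives estimates of opposite sign in 98% of trials. In about 56%, both are individually significant in opposite directions. A gradual fall with no jump and a 12-month mean ratio of 1/2.6 gives slope power near 1 with a true level change of zero.

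**The case against.** The strongest reply is that a journal article leaves the choice of coefficient and the handling of multiplicity to the analysis plan, and that intercept and slope is the ordinary description of segmented regression. On the missing decider alone this has force. It does not remove the mismatch, because the article itself fixes both the two-parameter analysis and a power statement for something else.

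Sizing on a simple ratio and analysing with a fuller model is also common, and the level change is itself a log rate ratio. That is fair, but a fourfold variance difference is too large to pass over.

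Three stronger readings are tempting and not supported:
- **The trial runs two 5% tests and so inflates its error rate.** The analysis sentence mentions no test or significance level. The only 5% is in the sample size calculation, and a joint test is not excluded. The 0.08 to 0.10 is conditional on an either-can-decide rule.
- **A 6-month look adds another primary test.** One general sentence says "All outcome measures for the impact assessment will be assessed at baseline, 6 months, and 12 months post-intervention", but Table 1 lists the primary outcome only as pre and post, and records are gathered at baseline and 12 months.
- **The trial is underpowered.** At 1 presentation per child-year, power for the article's own effect size is ample for a step change. The defect is that the stated power is not the power of the planned analysis.

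**Conclusion.** The point holds in this form: the primary analysis has two parameters and no deciding contrast, and the 80% power is stated for a quantity that is neither of them. The fourfold variance ratio does not depend on the assumed rate. The power figures do. Either the baseline rate is the one that makes 80% correct, and a level-change test then has only about 0.13 to 0.25, or the rate is nearer 1 per child-year, and the 80% is itself wrong. Eligibility requires at least one ED presentation or admission in the previous 12 months, so an implied 0.016 to 0.060 per child looks low, but the article gives no rate to settle it. Opposite-sign results are a realistic possibility under a waning effect. All figures assume Poisson counts without overdispersion or autocorrelation. The problem remains with ED presentations alone, so it is separate from having three utilisation measures. It should be corrected before analysis.

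**What to change.** In the Aim 1 Data analysis section, name one deciding contrast for asthma-related ED presentations, the measure used for sizing, and test it once at two-sided 5%. One suitable choice is the rate ratio from the same time series model over the 12 months after enrolment, against the counts projected from the pre-enrolment segment (intercept change plus 6 times the monthly slope change). Report the intercept and slope changes with confidence intervals as descriptive. In the sample size calculation, restate the power or detectable effect for that contrast, with its assumed baseline rate, leaving enrolment unchanged.

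The cost is a few sentences and one linear combination from a model already planned. The downsides are real: intercept and slope can no longer each be claimed as primary, and the average contrast relies on extrapolating the pre-enrolment series. With only about 12 pre months it is less precise than the level change (SE 0.228 against 0.173), so it should be used with the multi-year history that the protocol plans.

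### Secondary questionnaire outcomes: the only correlation structure named is at the level of three LHDs (random effect, significance pre-test, GEE), and no child level is named for three measures per child

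*Protocol article*

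**What the plan says.** The Data analysis section under Aim 1 of the protocol article fixes four things for the questionnaire outcomes.

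- **Reason for the model:** "Since each participant will have three repeated measures over time, we will use multi-level regression analysis".
- **Fixed effects:** visit enters as "a fixed effect for the intervention status (0 = pre-intervention, 1 = 6-month post-intervention, 2 = 12-month post-intervention"). The second covariate is the date of entry, which does not vary within a child: "calendar time of enrolment into the intervention for each participant".
- **Random part:** "as well as a random effect of the Local Health District (LHD) to explore the degree of variation in the intervention effect by LHD", followed by a deletion rule: "Our final model will exclude the random term in the presence of a statistically non-significant random effect".
- **Clustering:** "We will also consider participants are clustered within each LHD and use generalised estimating equations (GEE) approach in the regression analysis".

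Study design and setting gives the number of LHDs as three. Health service use, the primary outcome, has its own interrupted time series analysis and is not touched by this point.

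**The concern.** The reason given for a multi-level model lies within the child, but each correlation device that is named sits at the LHD. Three questions follow.

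1. If the model is fitted as written, with no child level, what happens to the standard errors?
2. Can three LHDs support a variance component, a significance test on it, and a sandwich variance?
3. Can the named random effect do its stated job of exploring variation in the effect between LHDs?

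At stake are the conclusions on asthma control, quality of life, adherence and family experience. One route loses real improvements and another can produce false ones. The text does not say whether the GEE replaces the random-effect model, follows it once the term is dropped, or stands beside it.

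**Working it through.** **Inputs from the protocol article.** Three visits per child, three LHDs, 270 children analysed. The 270 comes from the sample size paragraph for the primary outcome: 317 × 0.85 = 269.45, so it is reproduced to within one child. No sample size, power or standard error is stated for the secondary outcomes.

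**Assumptions.** Complete data, total within-LHD variance 1, within-child correlation ρ = 0.3, 0.5 or 0.7, 90 children per LHD, visit as a three-level factor.

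**1. No child level: visit contrast (12 months against enrolment).** Model SE = √(2/270) = 0.086. True SE = √(2(1−ρ)/270). The test rejects when |Z| > 1.96/√(1−ρ).

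| ρ | Model SE | True SE | Ratio | Type I error | Power where a child-level analysis has 80% |
|---|---|---|---|---|---|
| 0.3 | 0.086 | 0.072 | 1.20 | 1.9% | 68% |
| 0.5 | 0.086 | 0.061 | 1.41 | 0.6% | 51% |
| 0.7 | 0.086 | 0.047 | 1.83 | 0.03% | 22% |

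The last column is Φ(2.80 − 1.96/√(1−ρ)), with 2.80 = 1.96 + 0.84. A simulation of 4,000 trials gave type I errors of 2.1%, 0.5% and 0.0%. These were the same with LHD intercepts in the model as without, so it is the missing child level that matters here, not removal of the LHD term.

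**2. No child level: between-child covariate (calendar time of enrolment).** With the LHD term dropped, the true SE exceeds the model SE by √(1+2ρ) = 1.26, 1.41, 1.55. Type I error is 2{1−Φ(1.96/√(1+2ρ))} = 12%, 17%, 21% (simulated: 12%, 17%, 20%).

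**3. GEE clustered on three LHDs.** With K equal clusters, the uncorrected sandwich variance of the visit contrast is (K−1)/K times the usual variance of a mean of K values. The Wald statistic is therefore √(3/2) times a t on 2 df, and it rejects when |t₂| > 1.96 × √(2/3) = 1.600. For 2 df, P(|t| > x) = 1 − x/√(2+x²), which gives 1 − 1.600/√4.561 = 25%. This does not depend on ρ. Simulations gave 23% to 26%, including 26% with an exchangeable working correlation. At ρ = 0.5 the mean SE was 0.044 against a true 0.061.

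With the K/(K−1) correction and t on 2 df (critical value 4.303) the level returns to 5%. For an effect of 2.80 true standard errors, which gives 80% power on a normal reference, the non-central t on 2 df gives 35%.

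**4. The significance pre-test.** Take a 5% F-test between three LHDs as the pre-test.

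- *Child level respected:* F is multiplied by 1 + 90τ/(ρ + (1−ρ)/3), where τ is the LHD variance. At ρ = 0.5 and τ = 0.01, 0.02, 0.05 the multipliers are 2.35, 3.70 and 7.75, and the term is kept in 28%, 44% and 68% of trials (simulated: 27%, 45%, 68%).
- *Child level ignored:* the multiplier is 1 + 2ρ + 270τ. At τ = 0 and ρ = 0.5 it is 2, and the term is kept in 22% of trials although there is nothing to find (simulated: 23%).
- *At τ = 0.04 (LHD SD 0.2):* the term is kept in 58% to 68% of trials with the child level and 78% to 80% without it.

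**5. Variation in effect between LHDs.** Even if the three LHD effects were known without error, their variance would rest on 2 df. The 95% limits for the SD run from √(2/7.378) = 0.52 to √(2/0.0506) = 6.3 times the estimate.

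**6. Limit of the child-level remedy.** If the effect does vary between LHDs with variance 0.01, then at ρ = 0.5 the true SE for inference to LHDs in general is √(1/270 + 0.01/3) = 0.084. A child-level analysis with SE 0.061 would reject in about 15% of trials.

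**The case against.** The strongest reply is that a child level may be implied. The model is called multi-level, repeated measures are given as the reason, and LHD is introduced as an addition. A condensed article need not list every level. This stands as far as it goes: steps 1 and 2 hold only if no child level is fitted. Against it, the text speaks of a single random term and names no child effect or cluster. Steps 3 to 5 stand whichever reading is right.

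Four stronger readings are tempting, and the document does not support them.

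- *The LHD term will probably be removed, leaving ordinary regression on 3 × 270 records.* With an LHD SD of 0.2 it is kept more often than not. What can be said is that the pre-test is unreliable in both directions.
- *GEE on three LHDs is invalid in any form.* The 25% belongs to an uncorrected sandwich with a normal reference, and the article states no variance estimator. With a correction and t on 2 df the level is about right and the cost is power.
- *The random effect is an intercept and so cannot describe variation in effect.* The text does not say intercept, and its stated purpose could describe a random slope. The difficulty is that three LHDs can hardly estimate either.
- *The article names two contradictory models.* GEE could be an addition or a fallback. The order is unclear, but no contradiction is shown.

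It is also fair that, without a child level, the visit contrast errs towards caution and loses power without creating false positives.

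Leaving detail to an analysis plan does not answer the point. The random effect, its deletion rule and the clustering unit are stated choices.

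**Conclusion.** The point holds for the secondary questionnaire outcomes, at moderate severity. The named structure puts its correlation devices on three LHDs and names none for the child.

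The error has no single direction. A standard uncorrected GEE on LHD gives about five times the nominal false-positive rate, and a corrected one gives up more than half the power. A model without a child level overstates the SE of the visit contrast by 20% to 83% and understates SEs for between-child covariates.

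The sizes rest on the assumed correlations, unit variance, complete data and equal LHDs. The direction in steps 1 and 2 is the same at every correlation tried. The GEE error does not depend on the correlation, but it does depend on the LHD sizes, which the protocol article makes proportional to catchment. The primary outcome is unaffected. A reader should not infer that the secondary standard errors are certain to be wrong: that depends on whether a child level was meant and which variance estimator is used.

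**What to change.** State one model for these outcomes:

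- a random intercept for child, or an unstructured within-child covariance over the three visits;
- visit as a three-level factor;
- LHD as a fixed effect, kept without a significance test;
- a visit-by-LHD interaction where variation in effect is to be explored.

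Delete the rule that removes the random term. If GEE is kept, cluster on child with LHD as a covariate, and say whether it is the main or a supporting analysis.

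The cost is analysis wording only, with no new data, visits or participants. The price is scope: inference is then to these three LHDs and not beyond, which should be said when the results are used to argue for state-wide scale-up.
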